#### Intervention 1: YAM in schools: primary outcome

Suicidal ideation among young adolescents in both intervention and control condition schools will be assessed using the Suicidal Ideation Attributes Scale (SIDAS) [32]. SIDAS is a 5-item self-report scale addressing attributes of suicidal thoughts: frequency, controllability, closeness to attempt, level of distress associated with thoughts and impact on daily functioning. Scores ≥ 21 indicate a high risk of suicidal behaviour among youths. In this study, the SIDAS score will be assessed at baseline and at 3-month and 12-month follow-up. If a student has elevated scores on suicidal ideation (≥ 21 out of a maximum score of 50) at baseline assessment, he/she will be referred to the closest locally available health services such as a primary care centre, district mental health hospital or the Hospital for Mental Health in Ahmadabad (tertiary specialised mental health hospital).

Depression symptoms will be assessed using the Patient Health Questionnaire-9 (PHQ-9), a 9-item self-report scale [33, 34]. The PHQ-9 will be administered to students in the intervention and control schools at baseline and 3-month and 12-month follow-up. PHQ-9 scores range from 0 to 27 with higher scores indicating greater symptom severity. Scores of 5, 10, 15 and 20 represent cut-offs for mild, moderate, moderately severe and severe depression, respectively. Students who meet criteria for severe depression (scores > 20 on the PHQ-9 scale) at baseline assessment will be referred to the closest locally available health services such as a primary health centre, district mental health hospital or the Hospital for Mental Health in Ahmedabad (tertiary specialised mental health hospital).

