### Adverse events

Even though the possibilities of adverse events directly related to the intervention are low, the SPIRIT study will maintain an incident register to record serious adverse events (SAEs) and adverse events (AEs). SAEs in this study are defined as attempted suicide, completed suicide, death due to other reasons or hospitalisation for an acute psychiatric crisis among students participating in the YAM intervention. AEs include emotional distress caused by a trial procedure (either the outcome assessments or the intervention delivery). Recognition of SAEs and AEs is a standard training module for all SPIRIT research team members. Ongoing identification of SAEs is monitored by the surveillance system data collection team. In the school-based intervention, information about any SAEs may be reported by parents, data collectors, teachers and/or school heads. For the community storage boxes, SAEs may be reported by the CHW and/or the attendant of the community boxes and/or any other community member. A protocol specifying questions for each SAE/AE has been established and each project team member trained in this protocol. Additionally, a protocol for reporting AEs to the Principal Investigator (PI), Data and Safety Monitoring Board (DSMB) and Institutional Review Board (IRB) is in place for the duration of the project.

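### The PHQ-9 referral trigger of > 20 misses a score of exactly 20, the protocol's own cut-off for severe depression, and both student referral rules are tied to baseline although both scales are repeated at 3 and 12 months

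*Protocol article*

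**What the plan says.** Everything on student referral stands in the protocol article under Intervention 1: YAM in schools: primary outcome.

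- **PHQ-9 scale and bands.** The total runs from 0 to 27, a larger total being worse. The bands are set this way: "Scores of 5, 10, 15 and 20 represent cut-offs for mild, moderate, moderately severe and severe depression, respectively".
- **PHQ-9 referral.** The rule reads: "Students who meet criteria for severe depression (scores > 20 on the PHQ-9 scale) at baseline assessment will be referred". The destination is local health services.
- **SIDAS risk threshold.** "Scores ≥ 21 indicate a high risk of suicidal behaviour among youths". No time point is attached to this statement.
- **SIDAS referral.** The trigger is a score of at least 21, "out of a maximum score of 50) at baseline assessment, he/she will be referred to the closest locally available health services".
- **Timing of the scales.** For the SIDAS: "In this study, the SIDAS score will be assessed at baseline and at 3-month and 12-month follow-up". The schedule for the depression scale is the same: "The PHQ-9 will be administered to students in the intervention and control schools at baseline and 3-month and 12-month follow-up".

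The Adverse events section defines serious events among YAM students (attempted or completed suicide, death from other causes, hospitalisation for an acute psychiatric crisis). For non-serious events it says: "AEs include emotional distress caused by a trial procedure (either the outcome assessments or the intervention delivery").

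**The concern.** There are two separate defects in the same safety rule.

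First, the PHQ-9 trigger does not match the cut-off given one or two lines earlier. If 20 opens the severe band, a strict inequality at 20 drops its lowest score. Field staff will apply the number as written.

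Second, both referral sentences name the baseline assessment, but the trial measures the same students with the same scales twice more. A student who first crosses either threshold at 3 or 12 months has been identified by the trial as high risk or severely depressed, and the article states no action.

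New cases after baseline are to be expected on the protocol's own reasoning. The section on the school-based intervention chose this age group because suicide rates begin to rise at 15 and because psychological problems often start in adolescence. What is at stake is the protection of minors, not the validity of the comparison between arms.

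**Working it through.** No sample-size or power formula applies. The check compares sets of scores and assessment times.

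**Inputs** (all from Intervention 1: YAM in schools: primary outcome)
- PHQ-9 range: 0 to 27, taken as whole-number scores.
- PHQ-9 severe cut-off: 20.
- PHQ-9 referral trigger: > 20, at baseline.
- SIDAS high-risk threshold: ≥ 21. SIDAS referral trigger: ≥ 21, at baseline.
- Assessments of each scale: baseline, 3 months and 12 months.

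**Step 1: PHQ-9 threshold**
- Severe band by the stated cut-off (score ≥ 20): 20 to 27, which is 27 − 20 + 1 = 8 scores.
- Scores that trigger referral (score > 20): 21 to 27, which is 27 − 21 + 1 = 7 scores.
- Difference: 8 − 7 = 1 score, namely 20. So 1 of 8 severe scores is not referred on the PHQ-9.
- With ≥ 20, the referral set is 20 to 27 and equals the severe band.

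**Step 2: which reading of the cut-off is right**
- The alternative is that each cut-off closes the band below it. A score of 5 would then not be mild, which is not how a severity cut-off is ordinarily read.
- The SIDAS rule in the same section uses an explicit ≥, and its trigger equals its risk threshold. The two scales are therefore handled inconsistently.

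**Step 3: timing**
- Assessments per scale: 3. Assessments with a stated referral action: 1. Without one: 3 − 1 = 2 of 3.
- Scale of exposure: the sample size section for intervention 1 plans 4557 students. Two follow-ups give at most 2 × 4557 = 9114 student-assessments per scale, before attrition, with no stated referral. This counts assessments, not students above a threshold.

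**Step 4: does another section close the gap?**
- *Adverse events*: triggered by an event, or by distress that a trial procedure caused; not by a score.
- *Intervention 3*: community health workers are trained to identify and refer people at risk, but only in intervention villages and with no stated link to school scores.
- *Comparison condition*: brochures listing services and helplines.
- *Data monitoring*: a board meeting twice a year, with no stated role in referring individual students.

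None of these is a score-based referral at follow-up.

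**The case against.** The strongest reply has four parts.

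1. **The > 20 may be a typing slip.** The operative condition is meeting criteria for severe depression, and the preceding sentence places that at 20. This is plausible as an account of how the error arose, but it does not make the rule safe to follow. The number in brackets is the one staff will use, and it is a decision threshold, not background text. It is fair that the defect is one point wide, and that a student scoring 20 who also reaches 21 on the SIDAS is referred anyway.

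2. **The follow-up gap may be a product of condensation.** A journal article shortens the full protocol, the Trial status section cites a data and safety monitoring plan that is not shown, and the article does not say that referral happens only at baseline. This limits what can be claimed: a follow-up rule may exist elsewhere. But the article does more than stay silent. It attaches baseline to both referral sentences, and the restriction stands as written.

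3. **Other safety provisions exist.** They do, and a missing stated referral is not the same as having no safety net. None of them acts on a score, however, and recording a serious event comes after the harm that referral is meant to prevent.

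4. **The change costs more than a few words.** Data are collected on paper and de-identified before entry, and recruitment began in July 2019. Referral at follow-up needs prompt scoring and identification of the student at two more rounds. A referral at 3 months also adds care before the 12-month outcome. These points are correct and belong in the cost. They do not outweigh acting on a measured risk in a minor.

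**Conclusion.** The point holds in both parts.

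- **Threshold: wrong as written.** A PHQ-9 of exactly 20 meets the stated severe cut-off and is not referred on that scale, which is 1 of 8 severe scores. This rests on whole-number scoring and on the ordinary reading that a cut-off opens its band.
- **Timing: a badly set rule that is cheap to improve.** For each scale, 2 of 3 assessments have no stated referral. This rests on the article alone; the full protocol may say more.

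Those affected are students with a PHQ-9 of exactly 20 and a SIDAS below 21, and students who first cross either threshold after baseline. Their number cannot be derived from the article. Of the two parts, the timing gap carries more weight. No bias is alleged, and sample size, alpha and the planned analysis do not change. The correction should be made because the rule protects adolescents in a suicide-prevention trial.

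**What to change.** 1. In the PHQ-9 referral sentence, replace > 20 with ≥ 20.
2. In both the SIDAS and the PHQ-9 referral sentences, replace the reference to the baseline assessment with: at any assessment (baseline, 3 or 12 months), in both arms alike.
3. If the full protocol already provides for referral at follow-up, bring the article's wording into line with it.

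**Cost.** The edit is one symbol and one phrase in two sentences. No new data are collected and the referral pathway already exists. In practice, paper forms must be scored promptly at the two follow-up rounds, and the linking record described under Data management used to reach the student. Since the trial is already recruiting, this is a change to running procedures. Expect a small number of extra referrals, and some added care in both arms between 3 and 12 months. Applying the rule identically in both arms keeps the procedure the same for each.

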##### Secondary outcomes

Data for secondary outcomes (Table 1) will be collected from process measures maintained by the SPIRIT research team, such as a log with all the schools approached for the intervention and a record of all the schools that agreed to implement the intervention (see Table 1 for further description of process measures).

##### Process measures

Focus group discussions will be conducted with YAM instructors to obtain more in-depth information on the acceptability, feasibility, and perceived impact of the delivery of YAM sessions in intervention schools.

#### Intervention 2 community storage facility for pesticides: primary outcome

The primary outcome for intervention 2 is the same as the primary outcome for the integrated suicide prevention programme - namely reduction in deaths due to suicides and attempted suicides, which will be measured by the surveillance system as described above.

##### Secondary outcomes

Data for secondary outcomes (Table 1) will be collected from data logs maintained by the SPIRIT research team, such as a log of all the villages approached for installation of storage boxes, number of villages that agreed to have the storage boxes, number of households that requested a storage box and number of households that were allocated a storage box.

Monthly log records of the CSF for pesticides (maintained by the facility manager) in the intervention villages will be analysed to evaluate its use. Additionally, survey responses from a structured questionnaire administered by trained data collectors among households in four villages (two control villages, two intervention villages) will be assessed to gain an understanding of current purchase, use and storage options for these pesticides. Additional information will be collected at follow-up about the acceptability and use of the CSF in the intervention villages.

##### Process measures

In-depth interviews and FGDs will be conducted with facility managers, relevant household members, and village heads to understand reasons for use and/or non-use of the community storage facility for pesticides in the intervention villages. A random sample from users (*n* = 5) and non-users (*n* = 5) of the storage facility will be interviewed in depth to identify implementation barriers and facilitators related to use of the community storage facilities.

#### Intervention 3: primary outcome

The primary outcome measure for intervention 3 is change in knowledge, attitude, skills and practice (KAP) among community health workers. Assessments of KAP will be conducted at baseline (pre-training) and post training in the intervention villages. In both intervention and control villages, KAP assessments among CHWs will be carried out at 6-month and 12-month follow-up.

Knowledge will be assessed using a self-report gatekeeper training questionnaire derived from previously validated questionnaires in gatekeeper training surveys [35], with one item adapted to Indian settings. The questionnaire consists of eight questions gauging knowledge about suicides and suicidal behaviour; talking to someone who is suicidal and arranging help; and ability to manage clients with a high risk of suicide in a timely and appropriate manner.

Skills will be assessed using eight multiple-choice questions adapted from the WHO mhGAP self-harm/suicide module [13]. Items focus on what to do when someone presents with ideas of self-harm/suicide, understanding co-morbidity as a risk factor, asking someone directly about self-harm, emergency management, best interventions, talking to a care-giver and other psychosocial interventions for self-harm/suicide.

Attitudes among the CHWs towards suicide prevention will be assessed using a 14-item attitude questionnaire developed initially in the USA by Herron et al. (2001) for suicide-prevention front-line health staff [36]. Items focus on how staff perceive responsibility for suicide prevention, on funding suicide prevention services, and on working with persons at risk of suicide and attempted suicide.

To measure how knowledge is translated into practice post-training, CHWs will be asked to maintain a diary recording details of identification, assessment and referral to health services of any clients who show possible suicidal ideation or risk of self-harm or suicide. After referral, each client is expected to be followed up by a CHW nine times over the course of next 12 months and notes of the client consultation will be documented by the CHW using a structured follow-up questionnaire. The diary provides a record of the number of persons a CHW has seen with suicidal ideation or risk of self-harm, and the number of people assessed by trained CHWs and referred to mental health professionals. The average time to complete the KAP questionnaire is 45 min and each follow-up questionnaire takes 20–25 min. The diary provides a record for the primary outcome of this intervention, namely the number of persons with risk of suicide identified, assessed and referred by trained CHWs to mental health professionals and followed-up by CHWs.

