### Measures

The primary outcome of the integrated suicide prevention programme is a reduction in suicides and attempted suicides in the intervention villages compared to control villages. In addition, each intervention has its own primary and secondary outcomes (Table 1).

**Table 1 Tab1:** Primary and secondary outcomes of specific interventions of the cluster-randomised controlled trial

Interventions	Primary outcome	Secondary outcomes
Intervention 1: suicide prevention in schools through the Youth Aware of Mental Health (YAM) intervention	Reduction in suicidal ideation at 3-month and 12-month follow-up among adolescents in intervention schools	▪ Proportion of schools that agreed to implement the YAM intervention of the total number of schools approached for implementation ▪ Of those schools that agreed to implement the YAM intervention, the proportion of schools that implemented the programme ▪ Proportion of adolescents in intervention schools who received the YAM programme out of total number of adolescents in the selected grade
Intervention 2: community storage facilities (CSF) for pesticides	Reduction in the number of suicides and attempted suicides in intervention villages at 12-month follow-up	▪ Proportion of villages of those that were approached that agreed to have the CSF ▪ Proportion of villages that agreed to have the CSF or provided for or arranged space to build the storage facility ▪ Proportion of households reached with promotion activities linked to community storage of pesticides; proportion of households that requested a community storage box; proportion of households that received a community storage box ▪ Proportion of households in the villages that used the boxes regularly
Intervention 3: community health worker (CHW) training for identification, support and management of people at risk of suicide or self-harm	Number of persons with suicidal ideation detected by trained CHWs and number of persons referred by CHWs to mental health professionals for care for suicidal ideation	▪ Proportion of health workers trained in intervention villages ▪ Improvement in knowledge, skills, attitudes and practice of CHW who received training ▪ Number of CHWs applying knowledge and skills obtained through the training programme in their day-to-day practice at 6-month and 12-month follow-up

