#### Specific analysis for each intervention

For intervention 1, differences in PHQ-9 and SIDAS scores at 12-month follow-up between students in the intervention and control arms will be calculated using a multilevel, linear effect model adjusting for clustering by villages as a random effect. We will analyse the SIDAS scores both on a continuous and categorical scale. Parameters for categorical variables will be either no ideation versus ideation or tertile scores (low/medium/high).

For intervention 2, all the secondary outcome data as per Table 1 will be analysed and presented as summary tables using count data and logs maintained by research team. Additionally, data from survey responses from a structured questionnaire from four villages (two control, two intervention) will be analysed pre and post intervention to evaluate pesticide purchase, storage options and acceptability and use of the CSF in the intervention villages.

For intervention 3, due to the ordinal nature of the data (knowledge, skills and attitude scales), multilevel ordered logistic regression (ordinal logistic regression) will be employed to assess change in knowledge, skills and attitude from baseline to follow-up in both intervention and control groups. Adjusted and unadjusted estimates will be reported as the proportional odds ratio or log odds coefficient. The number of persons with suicidal ideation detected and referred on by trained CHWs will be recorded as count data through logs and daily record registers. All the count data will be analysed using descriptive statistics.

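### The protocol names two different primary outcomes for intervention 3, and the detection and referral count in Table 1 has no planned comparison between arms

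*Protocol article*

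**What the plan says.** Three places in the protocol article name the primary outcome of intervention 3.

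- The section Intervention 3: primary outcome begins: "The primary outcome measure for intervention 3 is change in knowledge, attitude, skills and practice (KAP) among community health workers".
- Table 1, under Measures, gives as primary: "Number of persons with suicidal ideation detected by trained CHWs and number of persons referred by CHWs to mental health professionals". Its secondary column lists: "Improvement in knowledge, skills, attitudes and practice of CHW who received training".
- Further into the intervention 3 section, the text returns to the count: "The diary provides a record for the primary outcome of this intervention, namely the number of persons with risk of suicide identified". The sentence goes on to cover assessment, referral by trained CHWs and follow-up.

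The diary that supplies the count is introduced as follows: "To measure how knowledge is translated into practice post-training, CHWs will be asked to maintain a diary recording details of identification". Under Specific analysis for each intervention, the number detected and referred is again attributed to trained CHWs, and the section closes: "All the count data will be analysed using descriptive statistics". That section gives knowledge, skills and attitude a multilevel ordered logistic model of change from baseline in both groups.

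**The concern.** An outcome cannot be both primary and secondary for the same component. While both labels stand, the result presented as primary for intervention 3 can be settled after the data are seen, and the protocol would support either choice.

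The two candidates are also not interchangeable. KAP follow-up is planned in both arms, and three of its four elements have a model. The count is described only for trained workers and is only to be tabulated. If Table 1 is followed, the primary result of this component of a randomised superiority trial is a tally from one arm. Such a tally cannot separate what training added from what workers would have detected and referred anyway.

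**Working it through.** No figure is stated for this outcome, so there is nothing to recompute. The section Sample size for intervention 3 says that the worker numbers are not a sample size calculation, and it gives no effect size or power. The check sets the text side by side.

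**Step 1: which outcome is primary?**

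| Place | KAP | Detection and referral count |
|---|---|---|
| Table 1 (Measures) | Secondary | Primary |
| Intervention 3: primary outcome, opening sentence | Primary | Not mentioned |
| Intervention 3: primary outcome, diary text | Status not stated | Primary |

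The direct contradiction is between Table 1 and the opening sentence of the intervention 3 section. The diary text sides with Table 1 on the count, but it does not itself make KAP secondary.

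**Step 2: in which arm is the count defined?**

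- The description of intervention 3 gives the training to CHWs in the intervention villages. The Comparison condition section offers control residents only enhanced usual care.
- Table 1, the diary text and the analysis section all attach the count to trained CHWs. The diary is introduced as a measure taken after training.
- The sample size section gives about 416 CHWs in 62 intervention villages and 420 in 62 control villages, so 416 + 420 = 836 workers are enrolled.
- Under the stated definition about 416 of these 836 can produce a count. For the other 420 the outcome is not provided for.

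**Step 3: is a between-arm analysis planned for the count?** No. The analysis section limits count data to description.

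**Step 4: does KAP offer a between-arm comparison?**

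- Assessments at 6 and 12 months are stated for both arms, so a comparison at follow-up is available from data already planned.
- The baseline and post-training assessments are stated for intervention villages only, yet the analysis section models change from baseline in both groups. These two statements do not fit together.
- The model covers knowledge, skills and attitude. Practice, the fourth element of KAP, has none.
- Knowledge, skills and attitude each have their own instrument, and no composite score is defined. KAP as written is therefore not yet a single outcome.

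**The case against.** **The diary may be the practice part of KAP.** The outcome named in the opening sentence includes practice, and the diary is there to show knowledge turning into practice. This reading softens the tension within the intervention 3 section, and that much stands. It does not remove the conflict with Table 1, which lists improvement in practice together with knowledge, skills and attitudes as secondary and the count separately as primary.

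**No sentence says that control workers keep no diary.** The diary sentence names no arm, the referral half of the Table 1 outcome says only CHWs, and control CHWs consent to data collection. This also stands: the one-arm reading is an inference. It is a strong one, because three places tie the count to trained workers and none provides for a control count. Even if control diaries existed, no comparison is planned.

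**Stronger readings that the document does not support.**

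- A reader might infer an inflated type I error: two primaries each tested at 5% would give 1 − 0.95² = 9.75% if independent. The count is not tested, so there is no second p-value and the figure does not apply. The harm is selective choice of outcome.
- A reader might infer that the control count is zero by definition, so that any positive number looks like an effect. The document sets no zero against anything; the control count is simply not provided for.
- A reader might infer that the trial cannot show effectiveness, or that the control workers serve no purpose. The programme primary outcome comes from surveillance in both arms with its own model, and control workers are assessed on KAP under either label.

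**Conclusion.** The point holds for the intervention 3 component. The contradiction in naming the primary outcome is proved by the text, and an unseen analysis plan cannot make both statements true. That the count has no control arm rests on the assumption that only trained workers keep the diary, which the wording supports but does not state. That no between-arm analysis of the count is planned is explicit.

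The size is qualitative: two incompatible primaries, of which the one in Table 1 is defined for about 416 of 836 enrolled workers and cannot, as defined, estimate the effect of training. It should be corrected because the label decides which result is reported as primary. The main conclusion of the trial, on suicides and attempted suicides, does not depend on it.

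**What to change.** Name one primary outcome for intervention 3, in the same words, in Table 1, in both places in the intervention 3 outcome section, and under Specific analysis for each intervention. Two routes are open to the sponsor.

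**KAP as primary (the cheap route).** Specify one scale (knowledge, skills or attitude) and compare it between arms at 12 months with the multilevel ordinal model already planned. Reconcile the baseline: either state a KAP baseline in control villages or drop change from baseline in favour of the 12-month comparison. Relabel persons detected, assessed and referred as implementation outcomes described in the intervention arm, and say that they are not evidence of effect. The cost is rewording and a check that the registry entry agrees. The 12-month comparison needs no new data; a control baseline would, if none was taken. The downside is that the component primary describes workers rather than clients.

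**The count as primary.** Collect it in the same way, over the same period, in control villages, and replace the descriptive analysis with a between-arm count model that allows for clustering by village. This keeps a client-level outcome but requires diaries from about 420 control workers. Asking untrained workers to record detection may itself change what they do. Recruitment was under way when the article was written, so this route becomes harder the later it is chosen.
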